## Abstract

**Background::**

The transition from advanced Chronic Kidney Disease (CKD) to dialysis is a period of heightened vulnerability for many patients. Virtual monitoring of these patients could facilitate the communication of accurate and reliable data between patients and health care providers, helping to avoid unnecessary emergency department (ED) visits and facilitate more optimal dialysis starts.

**Objective::**

To determine whether the addition of the VIEWER (Virtual Ward Incorporating Electronic Wearables) platform to usual care will lead to a reduction in ED visits and hospitalizations and lead to an increase in perceived safety of virtual care among patients and providers.

**Design::**

This study is a national, pragmatic, multicenter randomized controlled trial comparing usual care alone vs usual care plus the VIEWER virtual care platform in patients with advanced CKD. Given the nature of the intervention, patients and care providers will not be blinded; outcome assessment and statistical analysis will be blinded.

**Setting::**

Five CKD clinics in 2 Canadian provinces (Manitoba and Ontario).

**Participants::**

Patients with advanced CKD not on dialysis (eGFR <15 mL/min/1.73 m^2^, 2-year kidney failure risk >40%).

**Measurements::**

Participants randomized to the intervention group will be provided with the VIEWER platform, comprised of a wireless blood pressure (BP) monitor, weight scale, transcutaneous O_2_ sat (SpO2) monitor, wearable motion tracker, and mobile tablet running the VIEWER application. The intervention group will be trained to use the VIEWER platform to complete a daily self-assessment via the app (BP, weight, O_2_ saturation, step count) and weekly Edmonton Symptom Assessment System Revised (ESAS-r) survey. These assessments will be integrated into clinical decision-making in multidisciplinary kidney health clinics. Participants will use the VIEWER platform for 12 months (or until dialysis initiation) in addition to receiving usual care.

**Methods::**

Intention-to-treat (ITT) approach will be used to compare the primary outcome between 2 study groups. Time to primary and secondary outcomes will be assessed using univariate Cox proportional hazards models and a Kaplan-Meier analysis with a log-rank test. The primary outcome is the time to first hospital admission and/or ED visit. The control is usual care (no exposure to VIEWER platform).

**Limitations::**

Some individuals may face challenges with technology adoption, which could affect participation. Those without Internet access are limited in their ability to take part in this study.

**Conclusions::**

This study will help determine whether virtual monitoring in advanced CKD patients can reduce ED visits and hospitalization.

**Trial registration::**

Clinicaltrials.gov; identifier: NCT05726526.

## Introduction

More than 1 in 8 Canadians have chronic kidney disease (CKD), and more than 1 in 3 adults over 65 suffer from CKD and its related conditions.^1,2^ The most common causes of CKD are diabetes and hypertension, and in patients with these conditions, the prevalence may be even higher.^
2
^ The risk of progression to kidney failure varies depending on CKD stage (G1-G5) and degree of albuminuria (A1-A3).^
3
^ Patients who develop kidney failure require the initiation of renal replacement therapy, usually dialysis.

The transition from advanced CKD to the start of dialysis is a period of heightened vulnerability for many patients and is associated with a high risk of Emergency Department (ED) visits, hospitalization, and emergent or suboptimal dialysis.^
4
^ Multiple factors are thought to contribute to this phenomenon, including frailty, multimorbidity, unexpected declines in kidney function, or sudden appearance of uremic symptoms.^4,5^

Novel interventions designed to monitor late-stage CKD patients at home may help identify and pre-emptively treat acute worsening of clinical status (eg, volume overload, acute worsening of uremic symptoms) in these patients, reducing the number of ED visits, hospitalizations, and suboptimal dialysis in this patient population. Such strategies have proven successful in abrogating adverse clinical outcomes in other chronic diseases such as heart failure (HF).^
6
^

The primary objective of this trial is to determine whether the addition of the VIEWER (Virtual Ward Incorporating Electronic Wearables) monitoring platform to usual care in patients with advanced CKD (eGFR <15 mL/min/1.73 m^2^) will lead to a reduction in ED visits and/or hospitalizations.

## Methods

### Trial Design

The VIEWER study is a national, pragmatic, multicenter randomized controlled trial conducted at 5 Canadian sites comparing usual care vs usual care + the VIEWER virtual care platform in patients with advanced CKD (eGFR <15 mL/min/1.73 m^2^). Given the nature of the intervention, patients and care providers will not be blinded; outcome assessment and statistical analysis will be blinded.

### Sample Size Considerations

Based on systematic reviews of the published literature, we estimate a 39% reduction in the hazard of an outcome event (ie, hazard ratio [HR] = 0.61 for intervention).^6,7^ Further assuming an event rate in the usual care group of 11.4% per month,^
7
^ an expected median follow-up of 12 months per patient, a censoring rate of 3% per month, patient attrition of 10%, 2-ided alpha = 0.05, and beta = 0.10 (90% power), we will require 340 patients total (170 per arm), 68 patients/site.

### Patient Population

The trial will be conducted at 5 sites across 2 Canadian provinces:

Seven Oaks General Hospital (SOGH), Winnipeg, Manitoba.St. Boniface Hospital (SBH), Winnipeg, Manitoba.Health Sciences Centre (HSC), Winnipeg, Manitoba.London Health Sciences Centre, London, Ontario.Scarborough Health Network (SHN), Scarborough, Ontario.

Inclusion and exclusion criteria are presented in Table 1. The goal is to be as pragmatic as possible in order to include the majority of patients who may be eligible candidates for the trial. Potentially eligible participants that do not meet eligibility criteria can be re-screened at a later date if eligibility changes.

**Table 1. table1-20543581251359736:** Summary of Inclusion and Exclusion Criteria.

Inclusion criteria	Exclusion criteria
1. >18 years of age. 2. Patient or primary caregiver can read and speak English. 3. Patient or patient’s substitute decision maker is able to provide informed consent. 4. Patient or primary care giver cognitively and physically capable and willing to use the VIEWER mobile application and perform self-measurements (ie, weight, BP). 5. Have stage 5 CKD (2 measurements of eGFR <15 mL/min/1.73 m^2^); eGFR will be calculated with the CKD-EPI equation^ 8 ^ 6. Followed in a multidisciplinary CKD clinic. 7. Have >40% chance of beginning dialysis in the next 2 years based on the Kidney Failure Risk Equation (KFRE)^ 9 ^	1. Inability of self- or caregiver-assisted self-monitoring using the VIEWER platform.

### Ethical Considerations and Privacy

This protocol received approval from the Research Institute Research Ethics Boards (REB) of the University of Manitoba (HS25046 (B2021:066)), St. Boniface Hospital (RRC/2024/2152), London Health Sciences Centre (2023-123692-86164), and Scarborough Health Network Research Institute (NEP-23-011). Informed consent was obtained from all individuals who agreed to participate in the study. All study data will be entered into a secure research database (REDCap), which is passcode protected and accessible only through the secure WRHA network at the University of Manitoba. Only the research team will have access to patient data, ensuring the privacy and security of all participants.

### Study Procedures

Study flow is presented in Figure 1.

**Figure 1. fig1-20543581251359736:**
[figure not shown]
Study flow: 340 eligible participants will be randomly assigned to either the intervention group (receiving usual care along with the VIEWER virtual care platform) or the control group (receiving only usual care). Participants will be followed for 1 year or until dialysis initiation. Participants in the intervention group will receive a wireless BP cuff, weight scale, transcutaneous O_2_ saturation (SpO_2_) monitor, wearable motion tracker, and a mobile tablet with the VIEWER application. They will be trained to use the VIEWER platform while continuing to receive usual care. Participants in the control group will receive usual care without additional devices or platforms. All participants will complete the UK Kidney PREM score (adapted for CKD) and the Health-related Quality of Life using KDQOL-SF via REDCap or paper forms at baseline, 3, 6, 9, and 12 months (or every 3 months thereafter until dialysis initiation). At the end of the study, virtual interviews or focus groups will be conducted with a subset of participants from the intervention group and health care providers.

### Recruitment

A research coordinator will work with renal clinic staff (ie, nurse, clinical clerk or physician) at each site to identify potential participants. Patients attending clinic will be asked by a member of their care team about whether they might be interested in the VIEWER study. A brief script describing the study in lay terms will be provided to the care team to facilitate this. If the patient agrees, the research coordinator will approach them and provide more detailed information on the trial and answer any questions. Patients will also have the option of meeting virtually with the study coordinator at a more convenient time if they prefer.

### Informed Consent

During the informed consent process, whether in-person or virtual, the patient will be provided ample time for questions and reflection, including the option to contact the research coordinator at a later date with further questions. Written informed consent will be obtained by means of the participant’s dated signature and the dated signature of the study coordinator. Patients will have the option of either virtual (via Redcap portal) or paper consent. During the consent visit, upon signing of the consent form, the study coordinator will review inclusion/exclusion criteria with the participants to ensure eligibility based on the screening form. Participant address will be collected during this meeting should they opt for study kit delivery by courier/delivery service. A copy of the signed consent form will be made available to the participant.

### Randomization

Randomization will be performed centrally within the REDCap database using randomization macros in statistical software (SAS 9.4). Patients will be randomized 1:1 to control vs VIEWER groups, stratified by site with block sizes of 8 to accommodate stratification.

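### One constant block size of 8 within each unblinded site would let staff who know it and keep count foresee up to about one allocation in five

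*Protocol article*

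**What the plan says.** All references are to the protocol article.

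- **Randomization.** "Patients will be randomized 1:1 to control vs VIEWER groups", "stratified by site with block sizes of 8 to accommodate stratification". No second size and no random variation is mentioned. The mechanism is central: "Randomization will be performed centrally within the REDCap database".
- **Trial Design.** "patients and care providers will not be blinded; outcome assessment and statistical analysis will be blinded".
- **Recruitment.** "A research coordinator will work with renal clinic staff (ie, nurse, clinical clerk or physician) at each site to identify potential participants". A member of the care team makes the first approach, and the coordinator then gives the detailed information.
- **Informed Consent.** Once the form is signed, "the study coordinator will review inclusion/exclusion criteria with the participants to ensure eligibility", using the screening form. Patients may take time and come back later.
- **Patient Population, Table 1.** Most entry criteria are measured or factual, but one calls for judgement: the patient or caregiver must be "cognitively and physically capable and willing to use the VIEWER mobile application". The text above the table allows re-screening at a later date.
- **Primary Analysis.** The comparison is Kaplan-Meier with a log-rank test and no covariates. Multivariate Cox regression appears only among the sensitivity analyses.

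**The concern.** In a permuted block of known, constant size, the last assignments follow from the earlier ones. Central allocation prevents anyone from looking up the next assignment, but it cannot stop a person who has seen the earlier ones from counting.

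The conditions for counting are partly present here. Clinic nurses work with the VIEWER portal every weekday, and the research team trains the intervention patients, so arms are known at the site. Each site runs a single sequence because nothing else is stratified. The same clinics find and approach patients, and the timing of entry is flexible. One entry criterion depends on a view of how well the patient would cope with the platform.

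If fitter or more technically able patients were brought forward when VIEWER was due, or others delayed, the arms would differ before treatment. The unadjusted primary comparison would carry that difference, and the Cox sensitivity analysis could correct only for what was measured.

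**Working it through.** **Inputs.** Block size 8 and ratio 1:1 (Randomization), so 4 + 4 per block; 340 patients and 68 per site (Sample Size Considerations); 5 sites (Patient Population). Check: 5 × 68 = 340.

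**The plan's own figure.** The article gives no predictability figure; its only related figure is N. The stated inputs are HR 0.61, 11.4% events per month, 3% censoring per month, 12 months, 90% power and 10% attrition. Schoenfeld's formula gives 173 events. With P(event) = λ/(λ+c) × (1 − exp(−12(λ+c))) and c = 0.03, the event probabilities are 0.651 (λ = 0.114) and 0.487 (λ = 0.0695), mean 0.569. Then 173/0.569 = 304, and 304/0.9 = 338, against 340 stated. Block size enters nowhere, so N and power are untouched.

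**Allocations that are certain.** There are C(8,4) = 70 equally likely blocks. The allocation at position k is determined if one arm already holds 4 of the first k − 1, which has probability 2·C(k−1,4)/70.

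| Position | Probability determined |
|---|---|
| 1 to 4 | 0 |
| 5 | 2/70 = 2.9% |
| 6 | 10/70 = 14.3% |
| 7 | 30/70 = 42.9% |
| 8 | 70/70 = 100% |

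The sum is 112/70 = 1.6 per block, or 1.6/8 = 20%. This agrees with the closed form 2m/(m+1) at m = 4. In 42.9% of blocks at least the last two allocations are certain.

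**At the planned site size.** 68 = 8 × 8 + 4. The final half block adds nothing, because positions 1 to 4 are never determined. Per site: 8 × 1.6 = 12.8. Trial: 5 × 12.8 = 64, and 64/340 = 18.8%.

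**Guessing.** Always naming the arm that is behind is right 5.33 times in 8 (66.6%) over complete blocks and 66.0% of the time at 68 per site, against 50% by chance.

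**Alternatives.** Simulated at 68 per site. Assumptions: sizes are drawn with equal probability, and the observer knows the set and every past allocation but not the order of sizes. End-of-site imbalance (difference between arms) is computed exactly by recursion over block starts.

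| Scheme | Certain | Lagging-arm guess right | Mean imbalance | Maximum imbalance |
|---|---|---|---|---|
| Fixed 8 | 18.8% | 66% | 1.03 | 4 |
| 4/6/8 | about 2.2% | 68% | 0.56 | 4 |
| 6/8/10 | about 1.7% | 66% | 0.70 | 4 |
| 8/10/12 | about 1.4% | 65% | 0.83 | 6 (probability 0.00015) |

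As a hand check, fixed 8 ends each site 4 patients into a block, so the mean imbalance is (32 × 2 + 2 × 4)/70 = 72/70 = 1.03. Smaller constant blocks are worse than 8: size 6 makes 1.5/6 = 25% certain, and size 4 makes 1.33/4 = 33% certain.

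**The case against.** The strongest case against runs as follows.

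- **The figure is an upper bound.** It needs someone who knows the size, knows where a block starts and logs every allocation in order. Knowing the arm of one's own patients is less than that. This stands.
- **Site knowledge of the size is not shown.** The article prints the size, but it reports consent in the past tense, so enrolment seems to have begun before publication. Concealment steps may be in the full protocol, which is not at hand, and the article's silence on them is no fault. This also stands. What remains is that the scheme is a stated choice, and one constant size is easier to deduce than a varying one.
- **Room for steering is limited.** eGFR and kidney failure risk are measured criteria. The care team only asks about interest, and the coordinator reviews eligibility. This stands in part, because approach, timing and the judgement of capability remain open to influence.
- **Other safeguards exist.** Allocation is central, outcome assessment and analysis are blinded, and a Cox sensitivity analysis is planned. These help, but none prevents selection at entry.
- **Varying the size does not stop guessing.** This is correct: accuracy stays near 65 to 66% with the larger mixes and rises to 68% with 4/6/8. The gain lies in removing certainty.

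A reader might go further and infer that allocation in this trial is in fact predictable, that patients have been steered, or that 8 is too small. The article supports none of these. It does not show that staff know or count the blocks, it gives no data on selection, and smaller constant blocks would be more predictable.

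**Conclusion.** The concern holds as a conditional design weakness. The defect is a single constant size, stratified by site alone and now in print, in a trial whose recruiting clinics are unblinded. Under full tracking, 20% of allocations in complete blocks are certain in advance, or about 64 of 340 (18.8%) at the planned 68 per site. With no one counting, the number exploited is zero. The article does not allow the true value between these to be placed.

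The effect on the hazard ratio cannot be estimated from the document. Nothing in the article is miscalculated or contradictory on this point. The change is cheap and worth making if randomisation is still open.

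**What to change.** **Remaining randomisations.** Replace the constant size with sizes drawn at random within site from a set averaging at least 8. 6/8/10 is a suitable example, and 8/10/12 is an alternative. Have the list generated and held outside the sites, and keep the new sizes out of site-facing documents until the trial closes. Switch at the end of each site's open block, so that no unfinished block leaves an imbalance behind. Avoid 4/6/8: it removes nearly as much certainty but makes guessing slightly easier.

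**Patients already randomised.** Tabulate baseline eGFR and kidney failure risk score, both already collected, by position in block and arm. The contrast of interest is VIEWER against control at positions 7 and 8 compared with positions 1 to 4. Read the table descriptively: few patients are involved, and these two variables do not capture technical ability. Someone outside the blinded analysis should prepare it.

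**Cost.** A new REDCap allocation table. Mean end-of-site imbalance does not worsen (0.70 for 6/8/10 and 0.83 for 8/10/12, against 1.03 now). The maximum stays at 4 with 6/8/10; with 8/10/12 a difference of 6 is possible but has probability 0.00015 per site. Sample size, power and analysis stay as they are.

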### Baseline Assessment

Baseline assessment will take place within 14 days of enrollment either virtually or in-person. During the baseline visit, the research coordinator will provide general instruction on how to complete the UK Kidney PREM and the KDQOL-SF via a virtual link. Baseline data collected will include sex, gender, race, age, eGFR, kidney failure risk equation (KFRE) score, patient-reported outcome measures (PROMs) (measured by KDQOL-SF questionnaire) and patient-reported experience measures (PREMs). Demographic characteristics, eGFR, and KFRE will be collected from patient charts/electronic medical record (EMR) and entered into REDCap; KDQOL-SF and PREM questionnaires will be completed by patients via REDCap.

### Intervention Group

Participants in the intervention arm will receive training on how to use the VIEWER software and associated devices during a training session. Participants will be able to contact the study team with follow-up questions at any time during workday hours, Monday to Friday via text, phone call, and video link.

### VIEWER Description

The VIEWER is a CKD-specific virtual care platform that integrates data from a wireless blood pressure (BP) cuff, weight scale, transcutaneous O_2_ sat monitor (SpO_2_), and wearable motion tracker. The patient-facing component of VIEWER (patient portal) is a custom application based on a mobile tablet that guides patients through a daily self-assessment routine using the connected devices. The BP measurements, weight and oxygenation (as surrogates of volume status), and step counts (as a surrogate of functional status) provide semi-continuous longitudinal data on patient physical status. In addition, patients are prompted to fill out a weekly symptom survey (Edmonton Symptom Assessment Score-revised; ESAS-r), a validated instrument of kidney failure symptoms.^
10
^ Patient data and ESAS scores are automatically uploaded to fully PHIA/HIPPA-compliant servers, where they are made available to the patients’ care team through a secure, web-based provider portal. Provider notifications (flags) are generated for out-of-range values (ie, BP, weights for volume management) and a secure messaging component allows for direct patient-provider communication. The VIEWER platform components are presented in Table 2.

**Table 2. table2-20543581251359736:** VIEWER Platform Components.

VIEWER platform components
The VIEWER virtual care platform used in this study will include the following components: 1. Mobile tablet loaded with the custom VIEWER mobile application that will act as a portal for patients to upload clinical data (from connected devices) and access data trends and secure text/video communication (between patient/provider). 2. Web-based provider portal accessible through any Internet browser via a secure login. 3. Bluetooth-enabled home weight scale, BP cuff, O_2_ saturation monitor, and wearable motion tracker. 4. Secure text and video messaging between patients and providers (nurses in each clinic for management of the virtual platform). 5. Secure data transfer over the Internet. 6. Option to enable push notifications as a reminder to perform daily assessments.

Participants will be trained to use the VIEWER devices and app by a member of the research team via video conferencing call with an in-clinic option available if needed. On the provider side, assigned nurses at each site will be trained as “superusers” of the provider portal. These users will check the VIEWER platform daily and respond as needed (Monday to Friday) for flags and patient messages and will respond or communicate as needed to the health care team as per local clinic standard operating procedures. Trends in measurements will be reviewed weekly with the most responsible physician. During routine clinic visits, trends in all objective and subjective measures will be made available to inform clinical decision-making. Consistent with our pragmatic design, we will not be prescriptive in how monitoring data are interpreted; rather, we ask that care teams regularly review this enriched data stream and incorporate that information in the context of their own protocols and clinical judgment.

In addition to using the VIEWER virtual care platform, patients in the intervention group will continue to see their multidisciplinary CKD care teams as per local standard of care, either virtually or in-person.

### Control Group

Patients randomized to the control group will see their multidisciplinary CKD care teams as per usual care, either virtually or in-person.

